## 12. Study Management

### 12.1 Oversight and monitoring

Composition of the coordinating center and trial steering committee and composition of the data monitoring committee, its role and reporting structure

This trial has been supervised by the TSC, which consists of experts in epidemiology, pediatrics, and infectious diseases. The main responsibilities of the committee include the supervision of study design, implementation, data analysis, and trial reports. The TSC will meet every 3 months. The Data Coordination Center (DCC) will mainly be responsible for the quality control of data and the implementation of randomization. The Data Security Monitoring Committee (DSMC) will monitor and record any security issues that occur with regard to participants during the trial and propose solutions. The DCC and DSMC will meet once a month. Furthermore, the DCC and DSMC will report to the TSC. Stakeholder and public involvement groups will not be permitted.

### 12.2 Adverse event reporting and harms

All adverse events observed by the investigators will be recorded and reported to the DSMC, highlighting any seriousness as required. Furthermore, any causality between intervention and adverse events will be recorded.

### **12.3 Frequency and plans for auditing trial conduct**

The Trial Management Team will meet every 3 months to review the implementation of the study. The independent monitor will make an on-site visit once a month and check the quality of the data, including inclusion and exclusion criteria, informed consent, original data, and the absence of data.

### **12.4 Plans for communicating important protocol amendments to relevant parties**

A substantial amendment is defined as an amendment to the protocol that is likely to have a significant effect on the safety of participants. Notification of all substantial amendments will be provided to the participants' guardians and ethics committees. Non-substantial amendments and any deviations from the protocol will be fully recorded using a breach report form. In addition, online trial registries will be updated accordingly.

### **12.5 Dissemination plans**

The results of the study will be completely reported in international peer-reviewed journals. Both positive and negative results will be disclosed. We hope that our findings provide a potential clinical significance.

### **12.6 Biological specimens**

Biological specimens will not be collected in this trial.

### **12.7 Confidentiality**

During the course of the study, data collected will be kept strictly confidential and only accessed by members of the trial team. Data will be stored in a secure database. In publications, no identifying details of participants will be reported. We will determine whether anonymized trial data can be used for meta-analyses based on discussion by the ethics committee.

### **12.8 Study schedule**

The project is proposed to be performed from June 2019 to September 2020. The researchers will follow the subjects daily until the study end-points are obtained or the trial must be terminated.

### **13. Ethics approval and consent to participate**

The Shengjing Hospital of China Medical University Medical Ethics Committee has approved the research plan and written informed consent has been formally obtained from all participants' guardians during screening. The research protocol was approved by the Shengjing Hospital of China Medical University Medical Ethics Committee (No. 2019PS503K).

### **14. Statistical analysis plan**

#### **14.1 Descriptive statistics and baseline characteristics**

We will conduct intention-to-treat (ITT) and per-protocol (PP) analyses. Descriptive statistics for all baseline characteristics will be reported for each group. Categorical variables will be presented as counts and percentages (%), while continuous variables will be presented as mean  $\pm$  SD or medians with quartiles (Q1-Q3). The baseline data include demographic information, pregnancy-related details such as the occurrence of cesarean section, the number of pregnancies and parity, history of a mother's disease, medication history, as well as the newborn's gender, birth weight, and Apgar scores.

#### **14.2 Analysis of Primary Outcomes**

The two primary outcomes include the time to achieve complete meconium evacuation and the time to complete enteral feeding. Outcomes are presented as median (Q1-Q3). The outcomes will be analyzed using an independent sample t-test or Mann–Whitney test. Meanwhile, a multiple linear regression model will be used to analyze the factors affecting primary outcomes, including gender, birth weight, history of a mother's disease, etc. For outcome differences between the treatment and control arms, the median difference and 95% confidence interval (CI) will be assessed using the Mann–Whitney U test and the Hodges–Lehmann method. The time to achieve complete meconium evacuation and full enteral feeding will be analyzed using Kaplan–Meier curves and log-rank tests. In the Kaplan–Meier analysis, the computation of the median time holds significant methodological importance.

Precisely, the median time to accomplish complete meconium evacuation and full enteral feeding are ascertained as the time point at which 50% of the study participants reach these predefined endpoints.

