## **11. Sample size and statistical power estimation**

The sample size estimate is based on our pilot study; the time of complete meconium evacuation was 1.4 days, 1.2 days, and 1.2 days earlier in the breast milk enema group than in the saline enema group at  $23 \text{ w} \leq \text{gestational age} < 28 \text{ w}$ ,  $28 \text{ w} \leq$

gestational age < 29 w, and 29 w  $\leq$  gestational age < 30 w, respectively. Given that  $\alpha = 0.05$ ,  $\beta = 0.2$ , standard deviation (SD) = 2, sampling ratio = 1 and taking a 20% drop rate into account, the required total sample size is 78, 108, and 108 premature infants in each gestational age, respectively. A website was used to calculate the sample size (<http://powerandsamplesize.com/Calculators/>).

| Gestational age               | Difference | $\alpha$ | $\beta$ | SD | Sample size | Loss of follow-up | Final sample size |
|-------------------------------|------------|----------|---------|----|-------------|-------------------|-------------------|
| 23W $\leq$ Gastinal age < 28W | 1.4d       | 0.05     | 0.2     | 2  | 64          | 20%               | 78                |
| 28W $\leq$ Gastinal age < 29W | 1.2d       | 0.05     | 0.2     | 2  | 88          | 20%               | 108               |
| 29W $\leq$ Gastinal age < 30W | 1.2d       | 0.05     | 0.2     | 2  | 88          | 20%               | 108               |

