### **14.5 Subgroup Analysis**

For all aforementioned statistical analyses, stratified subgroup analyses will be conducted based on gestational age to compare specific intra-group outcomes. Gestational age categories are 23 weeks  $\leq$  gestational age < 28 weeks, 28 weeks  $\leq$  gestational age < 29 weeks and 29weeks  $\leq$  gestational age < 30 weeks This approach is employed to assess nuanced differences within distinct gestational age subgroups, enabling a comprehensive evaluation of outcomes tailored to the developmental stage of the fetus.

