### **14.6 Statistical software**

A two-sided  $P < 0.05$  will be considered statistically significant. All analysis will be performed in SAS version 9.2 (SAS Institute Inc., Cary, NC, USA) and SPSS version 22.0 (IBM Inc., Chicago, IL, USA) software. Interim analyses are not planned.

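### Two primary outcomes are each judged at two-sided P<0.05 with no success rule, so the chance of a false positive on the two overall tests is about 7-10%, and the status of the separately sized gestational-age strata is unclear.

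*Protocol*

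**What the plan says.** - **Outcomes.** Protocol section 8.1 lists two primary end-points, and section 14.2 repeats them: "The two primary outcomes include the time to achieve complete meconium evacuation and the time to complete enteral feeding". Neither section ranks them or says whether one or both must succeed.
- **Threshold.** Section 14.6: "A two-sided $P < 0.05$ will be considered statistically significant". No analysis is exempted. No interim analysis is planned, so no further alpha is spent that way.
- **Sample size.** Section 11 makes three separate calculations, each at alpha 0.05 and beta 0.2: "the required total sample size is 78, 108, and 108 premature infants in each gestational age, respectively". The assumed effects are for meconium only: "the time of complete meconium evacuation was 1.4 days, 1.2 days, and 1.2 days earlier in the breast milk enema group". No calculation is given for full enteral feeding.
- **Strata.** Section 14.5: "For all aforementioned statistical analyses, stratified subgroup analyses will be conducted based on gestational age to compare specific intra-group outcomes". Both primary outcomes are therefore analysed overall and again in each of the three strata that section 11 sized.
- **Methods.** Section 14.2 first allows a t-test or a Mann–Whitney test. It then assigns Mann–Whitney with Hodges–Lehmann to the difference between arms, and adds log-rank tests without ranking them against it. Section 14.1 plans ITT and per-protocol analyses and does not say which is primary.

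**The concern.** A 5% threshold protects the trial's conclusion only if there is one decisive test or a rule that combines several. Here either primary outcome could be reported as positive at 0.05, so the error rate of the conclusion exceeds the stated 5%.

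The protocol is also inconsistent about where the confirmatory comparison lies. Section 11 reads like three stand-alone trials on one outcome, section 14.2 like one trial on two outcomes, and section 14.5 treats the separately powered strata as subgroups. A positive trial could mean either overall test, both, or any one stratum, and each reading has a different error rate. If this is not settled before the data are seen, the choice can follow the results.

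**Working it through.** **1. The plan's own figures (section 11).** Inputs: differences of 1.4, 1.2 and 1.2 days, SD 2, 1:1 allocation, alpha 0.05, beta 0.2, 20% loss. I take the test as two-sided, as in section 14.6.

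n per arm = 2 × SD² × (1.960 + 0.842)² / difference²

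- 1.4 days: 2 × 4 × 7.849 / 1.96 = 32.04, so 33 per arm, 66 in total (plan: 64)
- 1.2 days: 2 × 4 × 7.849 / 1.44 = 43.6, so 44 per arm, 88 in total (plan: 88)
- With 20% loss: 64 / 0.8 = 80 and 88 / 0.8 = 110 (plan: 78 and 108)

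Agreement is within 2 infants throughout. Each stratum is thus sized at an unsplit two-sided 0.05, on meconium time alone.

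**2. Two overall tests.** If the outcomes were independent, the chance of at least one false positive is 1 − 0.95² = 9.75%. For correlated outcomes I simulated under the global null, where breast milk affects neither outcome. The three strata are independent and weighted 78:108:108, each overall test is the weighted combination of its strata, and the two outcomes have correlation ρ. The protocol gives no ρ, so the range is an assumption.

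**3. Eight tests.** These are two outcomes, each tested overall and in three strata. The formula for eight independent tests, 1 − 0.95⁸ = 33.7%, does not apply, because each overall test is built from its own strata. The simulation allows for this.

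| Assumed ρ | Two tests, either direction | Two tests, favouring breast milk | Eight tests, either direction | Eight tests, favouring breast milk |
|---|---|---|---|---|
| 0 | 9.7% | 4.9% | 29.6% | 15.8% |
| 0.5 | 9.1% | 4.5% | 27.7% | 14.5% |
| 0.7 | 8.3% | 4.2% | 25.5% | 13.3% |
| 0.8 | 7.8% | 3.9% | 24.0% | 12.4% |
| 0.9 | 7.1% | 3.6% | 21.9% | 11.3% |

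The benchmarks for a single two-sided 0.05 test are 5% in either direction and 2.5% in favour of breast milk.

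**4. What controlling alpha would cost.** This uses the whole sample and a normal approximation, with SD 2 as the within-stratum SD.

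- Evaluable infants: 0.8 × 294 = 235
- Average difference: (78 × 1.4 + 216 × 1.2) / 294 = 1.25 days
- Standard error: 2 × √(4 / 235) = 0.261; ratio 1.253 / 0.261 = 4.80
- Power at 0.05: Φ(4.80 − 1.96) = 99.8%
- Power at 0.025: Φ(4.80 − 2.24) = 99.5%
- If the true effect were half the pilot effect (my assumption): ratio 2.40, power Φ(2.40 − 1.96) = 67% at 0.05 and Φ(2.40 − 2.24) = 56% at 0.025

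**The case against.** - **Two primary outcomes need no adjustment if both must succeed.** This is correct as statistics, but the protocol states no such rule.
- **A separate SAP may settle it.** It may. However, section 14 is itself titled as the statistical analysis plan and fixes the threshold for all results. The point concerns a rule the document states, and that rule does not hold the error at 5%.
- **Subgroup analyses are ordinarily supportive.** This largely stands. A reader might take 22-30% as the trial's error rate, but the documents do not support that: the figure applies only if a stratum result may carry a claim. Section 11's separate sizing leaves that possible and nothing rules it out, so the status needs stating.
- **The errors that matter are those favouring breast milk.** This stands, and those rates are about half the two-directional ones. For the two overall tests they are 3.6-4.9%, still above the 2.5% of a single test.
- **Further readings that do not stand.** A reader might infer that the smallest P-value among t, Mann–Whitney and log-rank may be chosen. No text permits that, and section 14.2 names Mann–Whitney with Hodges–Lehmann for the arm difference, although log-rank stands beside it unranked. A reader might also infer that all three strata must succeed, or that strata are to be compared with each other through their separate P-values. The protocol states no such rule, and section 14.5 speaks of differences within subgroups.

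**Conclusion.** The point holds. With two primary outcomes, one threshold and no success rule, the chance of a false positive on the two overall tests is about 7-10% instead of 5%, for assumed correlations from 0.9 down to 0. About half of that favours breast milk. The rate over eight tests, 22-30% on the same range, is conditional on stratum results being allowed to support a claim. The contradiction between sections 11 and 14.5 leaves that condition open. The rates rest on the global null and on one decisive test per outcome and population. They do not count any extra P-values from the log-rank or per-protocol analyses.

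**What to change.** - **Section 14.2:** name one decisive between-arm test per primary outcome, in the whole ITT sample, stratified by gestational age. Control the overall alpha at 0.05, for example by testing meconium time at 0.05 first and full enteral feeding at 0.05 only if the first succeeds. Splitting the alpha at 0.025 each is equally acceptable. Label the other tests supportive.
- **Section 14.5:** state that the stratum results are supportive and will be reported with estimates and confidence intervals, without separate significance claims.
- **Section 11:** state that the power calculation covers meconium time only.

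The cost is wording; no further infants are needed. With the fixed order, feeding cannot be claimed if the meconium test fails. That is unlikely on the plan's inputs (99.8% power) but a real risk if the pilot effect is overestimated (67% at half the effect). The split avoids that dependence and still leaves 99.5% power for meconium time on the plan's inputs, but it tests feeding at 0.025. The choice should be made before outcome data are seen.

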## 1. Background

According to estimates, 15 million premature births occur every year worldwide. China has the second largest number of premature infants in the world, 1.17 million premature births are reported in China every year, accounting for 10% of all newborns. Delayed action of full enteral nutrition in preterm infants is closely associated with an increase in morbidity and mortality. Delayed meconium evacuation is a recognized cause of intestinal dysfunction, which can cause delayed feeding, gastric retention, and feeding intolerance in preterm infants. The immature intestinal motility mechanism and neurotransmitter system of low-birth-weight infants delay meconium evacuation. Moreover, viscous meconium causes functional blockage of the intestines and abnormal gastrointestinal functions. The younger the gestational age of premature infants, the later and longer the meconium evacuation. Studies have shown that early meconium evacuation improves feeding intolerance and promotes weight gain. Because the meconium contains high levels of bilirubin, a delay in meconium evacuation increases the intestinal circulation of bilirubin, thereby aggravating neonatal jaundice and increasing the risk of bilirubin brain damage, kernicterus, serious sequelae, and even death.

Currently, the widely used strategies for inducing meconium evacuation worldwide are glass rod stimulation of the rectum, enema with formulations and oral intake of glucosamine (Gastrografin). Among them, enemas are the most commonly used approach. The formulations used for enemas include solutions (including physiological saline, glycerin, and diatrizoate) and suppositories (mainly glycerin). Glucosamine, a formulation for meconium evacuation that has emerged in recent years, is a gastrointestinal contrast agent that can be administered orally or rectally and has a hyperosmotic effect. However, the effects of glucosamine in meconium evacuation remain controversial. Glycerin solutions and glycerol suppositories have been widely used abroad as enema formulations, although a meta-analysis has suggested that the effects of glycerol solutions or glycerol suppositories in preterm

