### **5. Randomization**

Participants will be allocated to intervention and control groups with stratified block randomization using a computer-generated randomization list by an independent statistician not otherwise involved in the trial. The participants will be stratified based on gestational age. Then, the participants will be assigned in a randomized block design to the intervention and control groups in a 1:1 ratio. Block size will be 4 and 6 to ensure equal numbers of participants in the intervention and control groups. At the beginning of the trial, random sequence will generate a set of study numbers. Each study number will be paired with a method of intervention and sealed in an opaque envelope. The envelopes will be grouped based on gestational age. Recruited

participants will be allocated to intervention or control groups by selecting an envelope. The program will be set up using SAS 9.2 (SAS Institute Inc., Cary, NC).

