### **14.3 Analysis of Secondary Outcomes**

The secondary outcomes will include the hospitalisation days, weight at the time of discharge, and duration of TPN. The outcomes will be analyzed using an independent sample t-test or Mann–Whitney test. Meanwhile, a multiple linear regression model will be used to analyze the factors affecting primary outcomes, including gender, birth weight, history of a mother's disease, etc. Outcomes are presented as median (IQR). For outcome differences between the treatment and control arms, the median difference and 95% CI will be assessed using the Mann–Whitney U test and the Hodges–Lehmann method.

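### Randomisation is stratified by gestational age, but the pooled primary comparisons name no strata, so confidence intervals are too wide and the tests conservative

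*Protocol*

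**What the plan says.** **Design.** Protocol section 5 states: "The participants will be stratified based on gestational age". Within strata, infants are "assigned in a randomized block design to the intervention and control groups in a 1:1 ratio", and "Block size will be 4 and 6". Section 1 gives the reason this factor matters: "The younger the gestational age of premature infants, the later and longer the meconium evacuation".

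**Primary analysis.** Section 14.2 states: "The outcomes will be analyzed using an independent sample t-test or" a Mann–Whitney test. The median difference and its interval "will be assessed using the Mann–Whitney U test and the Hodges–Lehmann method". Kaplan–Meier curves and log-rank tests are added. None of these is described as stratified. A multiple linear regression is also planned, but to study factors that affect the outcome. It names gender, birth weight and maternal disease in an open-ended list, without gestational age, and is not presented as the source of the treatment effect.

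**Where gestational age does appear.** Section 14.5 repeats the analyses separately in three bands (23 to <28, 28 to <29 and 29 to <30 weeks). Section 11 sizes the trial separately in the same three bands. Section 4.1 defines two groups (23 to <28 and 28 to <30 weeks), and section 4.2 recruits 78 and 216 infants to them. Section 5 does not list the strata.

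**Secondary outcomes.** Section 14.3 states: "The secondary outcomes will include the hospitalisation days, weight at the time of discharge, and duration of TPN". They get the same unadjusted two-group tests. Its regression sentence names birth weight but refers to the primary outcomes.

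**The concern.** Stratified 1:1 allocation balances the arms on gestational age. The chance error in the treatment difference then comes almost entirely from variation within strata. An unstratified t-test or rank test estimates its error from total variation, which also contains the differences between strata. If gestational age is prognostic, as the protocol says for meconium evacuation, the reported standard error is larger than the true one. The interval is then wider than it need be, and the test rejects a true null less often than 5%.

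What is at stake is precision in the headline estimate and power against an effect smaller than planned. The subgroup analyses in section 14.5 do not repair this: they give three separate results and no combined stratified one.

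**Working it through.** **Inputs.** From section 11: within-band SD 2 days; differences 1.4, 1.2 and 1.2 days; band totals 64/88/88 before dropout (240) and 78/108/108 after (294). From section 14.6: two-sided 5%. The mean outcome in each band is not given, so the band means below are assumptions, shown as a range.

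**The plan's own figure.** Per arm, n = 2 × (1.96 + 0.84)² × 2² / difference². For 1.4 days this is about 32 before rounding, or 64 in total (66 if each arm is rounded up). For 1.2 days it is 44 per arm, or 88. Power at the stated totals is 80.0% and 80.4%. The stated sizes therefore reproduce, and they rest on variation within a band only.

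**Formulas for the pooled test.** Let B be the between-stratum variance with weights 78/108/108 out of 294.
- Inflation of the variance estimate: f = (4 + B) / 4.
- Interval too wide by √f − 1.
- True size: 2 × [1 − Φ(1.96 × √f)].
- Power where a stratified test has 80%: Φ(2.80 − 1.96 × √f).
- Power at the planned effect: Φ(d/SE − 1.96 × √f), with d = (78 × 1.4 + 216 × 1.2)/294 = 1.253 days and SE = 2 × 2/√240 = 0.258, so d/SE = 4.85.

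Example, means 2/1/0: overall mean 264/294 = 0.898; mean square 420/294 = 1.429; B = 1.429 − 0.898² = 0.62; f = 1.156; √f = 1.075.

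| Assumed band means (days) | B | Interval too wide by | True size | Power where stratified has 80% | Power at planned effect, 240 analysed |
|---|---|---|---|---|---|
| 0/0/0 | 0 | 0% | 5.0% | 80% | 99.8% |
| 1/0/0 | 0.19 | 2.4% | 4.5% | 79% | 99.8% |
| 2/1/0 | 0.62 | 7.5% | 3.5% | 76% | 99.7% |
| 3/1/0 | 1.40 | 16% | 2.3% | 70% | 99.5% |
| 4/2/0 | 2.49 | 27% | 1.3% | 62% | 99.1% |

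**Simulation check.** 10,000 trials per scenario were run with no treatment effect, normal outcomes, strata of 64/88/88 and permuted blocks of 4 and 6. At shifts of 0, 1 and 2 days per band, the t-test rejected in 5.2%, 3.5% and 1.4% of trials and the Mann–Whitney test in 5.2%, 3.6% and 1.3%. A linear model with stratum terms rejected in 5.0% to 5.2% throughout. The log-rank test was not simulated.

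**If randomisation uses two strata rather than three.** Only the variance between the two groups is removed by design. With band means 2/1/0, the group means are 2 and 0.5 and the removed variance is (78 × 216/294²) × 1.5² = 0.44. The remainder of B, 0.62 − 0.44 = 0.18, stays within strata. Then f = 4.62/4.18 = 1.105, the interval is 5% too wide and the size is about 3.9%.

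**The case against.** The strongest case against has four parts.

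- **The harm is small at the planned effect.** This stands. The pooled test keeps more than 99% power at shifts of 1 to 2 days per band, and 96.5% even at 3 days.
- **Gestational age is handled elsewhere.** This stands in part. The trial is sized per band, and the analyses in section 14.5 are free of between-band variation. They are labelled subgroup analyses, however, and yield no combined estimate.
- **The size rests on assumed means.** This stands. With no difference between bands there is no loss, and 1/0/0 costs almost nothing. The prognostic statement in section 1 also concerns meconium evacuation, not full enteral feeding.
- **Strata may be left to a separate analysis plan.** This does not stand as a full answer. Section 14 carries the title of a statistical analysis plan and names the tests. The point concerns the tests it names, not a missing detail.

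Three stronger readings are tempting, and the documents do not support them.

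- A reader might infer that off-nominal error rates mean too many false positives. The departure is only downward.
- A reader might multiply 294 by f and conclude that 340 (2/1/0) or 397 (3/1/0) infants are needed to match a stratified analysis. Those figures match interval width only. After stratified allocation, the unadjusted difference has essentially the same true variance as the stratified one. Matching 80% power needs 294 × [(1.96 × √f + 0.84)/2.80]², about 326 and 364. Both figures also start from the enrolled number, not the 240 planned for analysis.
- A reader might say that gestational age is excluded and birth weight ignored. Section 14.2 names birth weight, a likely partial proxy for gestational age, and its list is open-ended. Gestational age is unnamed, not ruled out.

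**Conclusion.** The point holds as a matter of efficiency, not validity. The pooled primary comparisons do not use the factor on which randomisation is stratified, so the stated precision is worse than the design delivers. Under the assumed means 1/0/0, 2/1/0 and 3/1/0, the interval is about 2%, 7.5% and 16% too wide and the true size about 4.5%, 3.5% and 2.3%. These figures assume a within-stratum SD of 2 days, roughly normal outcomes and three balanced strata, which section 5 does not confirm.

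At the planned 1.2 to 1.4 days the practical cost is mainly interval width. Power suffers if the true effect is smaller: where a stratified test would have 80%, the unstratified one has 76% at a 1-day shift per band and 62% at 2 days. Full enteral feeding is the outcome most exposed, to the extent that it also varies with gestational age, because no sample size was calculated for it. The change is worth making because it costs almost nothing.

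**What to change.** 1. In section 14.2, make the pooled treatment comparison for each primary outcome stratified by the gestational-age strata used at randomisation. Suitable forms are a stratified log-rank test with a stratified Cox model; a van Elteren test with a stratum-aligned Hodges–Lehmann estimate and interval; or a model with treatment and stratum terms. Choose one as decisive for each outcome.
2. In section 5, state whether randomisation uses the two groups of section 4.1 or the three bands of sections 11 and 14.5, and use the same strata in the analysis.
3. In section 14.3, report the treatment effect on discharge weight from a model with birth weight and gestational-age stratum. The between-arm comparison there is unadjusted, and the regression sentence refers to primary outcomes.

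The cost is a few sentences and a few lines of code. Gestational age and birth weight are already collected at baseline (section 9.1), and the sample size does not change.

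### Section 14.2 plans both Mann–Whitney and log-rank for each primary outcome at P < 0.05 and names neither as decisive; if either may carry the claim, the error per outcome is about 7–8%

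*Protocol*

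**What the plan says.** Protocol Section 14.2 covers both primary outcomes together: "The two primary outcomes include the time to achieve complete meconium evacuation and the time to complete enteral feeding". It names between-arm tests in three places.

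- First: "The outcomes will be analyzed using an independent sample t-test or" a Mann–Whitney test. The two are alternatives, and no rule for choosing is given.
- Second, for the difference between arms, the median difference and its 95% CI "will be assessed using the Mann–Whitney U test and the Hodges–Lehmann method". No condition is attached.
- Third, the same two outcomes "will be analyzed using Kaplan–Meier curves and log-rank tests". No condition is attached here either.

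A multiple linear regression is also mentioned, but for factors affecting the outcomes, so it is left aside here.

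Section 14.6 states that a two-sided P < 0.05 "will be considered statistically significant", without tying this to a particular test. It adds "Interim analyses are not planned", so no error is spent on interim looks. Section 14.5 repeats all the analyses within three gestational-age groups. Section 11 sizes each of those groups separately, from a mean difference and an SD of 2 d.

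**The concern.** Mann–Whitney and log-rank both compare the arms on the same outcome, but they weight early and late times differently and are not perfectly correlated. With two tests at 0.05 and none in charge, two things can go wrong. A claim can rest on whichever test is significant, which takes the error above the stated level. Or the tests can split, and the protocol gives no way to say whether the trial succeeded. The open choice between t-test and Mann–Whitney adds a little more freedom. All this happens within each primary outcome. The presence of two primary outcomes and of three gestational-age groups are separate matters and are not counted here.

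**Working it through.** **Inputs from the protocol.** Section 11: differences 1.4, 1.2 and 1.2 d; SD 2 d; 1:1 allocation; α = 0.05; β = 0.2; 20% drop-out; totals 64, 88 and 88 before drop-out and 78, 108 and 108 after. Section 14.6: two-sided 0.05.

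**Assumptions.** Times are normal or lognormal with mean 7 d and SD 2 d (the mean and the shapes are not in the protocol). Every infant reaches the endpoint, so there is no censoring.

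**1. The plan's own figure.** n per arm = 2 × (1.960 + 0.842)² × SD² / δ².
- δ = 1.4: 2 × 7.849 × 4 / 1.96 = 32.04, total 64.1 (stated 64).
- δ = 1.2: 2 × 7.849 × 4 / 1.44 = 43.60, rounded up to 44, total 88 (stated 88).

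Dividing by 0.8 gives 80 and 110, against 78 and 108 stated, a difference of 2 infants. So 32 and 44 per arm fit a two-sided 5% comparison of two means with about 80% power.

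**2. Pooled figures.** Final total 78 + 108 + 108 = 294, and 294 × 0.8 = 235.2, about 118 per arm. Average planned effect: (64 × 1.4 + 88 × 1.2 + 88 × 1.2) / 240 = 300.8 / 240 = 1.25 d.

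**3. No true effect** (8,000 trials per row; all tests on the same data, each at 0.05):

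| Times | Per arm | Mann–Whitney | Log-rank | Either of these two | Any of three, with t-test |
|---|---|---|---|---|---|
| normal | 32 | 4.7% | 5.5% | 7.3% | 8.1% |
| normal | 44 | 4.8% | 5.3% | 7.2% | 7.7% |
| normal | 120 | 4.8% | 4.9% | 7.2% | 7.8% |
| lognormal | 32 | 5.2% | 5.6% | 7.6% | 8.0% |
| lognormal | 44 | 5.1% | 5.4% | 7.7% | 7.9% |
| lognormal | 120 | 4.9% | 5.3% | 7.3% | 7.5% |

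Simulation error is about √(0.075 × 0.925 / 8000) = 0.3 percentage points. Each test alone is close to 5%; the excess comes from having a choice.

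**4. Planned effects within strata** (4,000 trials per row):

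| Times | Per arm, effect | Mann–Whitney power | Log-rank power | The two disagree |
|---|---|---|---|---|
| normal | 32, 1.4 d | 77.6% | 73.0% | 13.5% |
| normal | 44, 1.2 d | 76.8% | 71.2% | 13.9% |
| lognormal | 32, 1.4 d | 82.2% | 65.5% | 18.6% |
| lognormal | 44, 1.2 d | 82.7% | 65.3% | 18.9% |

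Further runs of the lognormal scenario came out near 20%, so about 19–20% is a fair summary.

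**5. Planned effect, pooled** (118 per arm, 1.25 d): Mann–Whitney power is above 99%, and the two tests disagree in about 1% (normal) to 2% (lognormal) of trials.

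**The case against.** **The protocol leans towards one test.** Outcomes are presented as medians, and the arm difference is tied to Mann–Whitney with Hodges–Lehmann. A reader might infer that three tests will be run on every outcome. The text does not support that, because the t-test is only an alternative to Mann–Whitney. This objection stands, and the size is therefore stated for two tests. It does not remove the point: log-rank is planned for the same outcomes just as firmly, and nothing ranks it below Mann–Whitney.

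**The 5% level is not shown to be broken.** A reader might infer that the plan as written fails to hold 5%. The protocol nowhere says that one significant test is enough, so the excess arises only if that is allowed. Nor is the excess as large as three independent tests would give (1 − 0.95³ = 14.3%), since these tests are strongly correlated.

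**Disagreement is rare in the pooled sample.** This also stands at the planned effect. Disagreement of 15–21% in the pooled sample appears only at a true shift of about 0.7 d, roughly half the planned one. The strata still matter, because Section 11 powers each one separately and Section 14.5 repeats every analysis in each.

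**Infants who never reach the endpoint.** Log-rank can censor them, whereas a t-test or Mann–Whitney needs some other handling. That is a further reason to choose in advance, but the simulations contain no such infants, so the figures do not measure it.

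**A separate analysis plan might settle this.** It might. But Section 14 is itself titled a statistical analysis plan and fixes these tests, so the ambiguity lies in what the protocol states.

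**Conclusion.** The point holds in this form: two unconditional tests per primary outcome, plus an open t-test alternative, share one 0.05 threshold and none decides. If either Mann–Whitney or log-rank may support a claim, the error per outcome is about 7–8%. At the planned effects within strata the two tests give different verdicts in about 13–14% (normal) to 19–20% (lognormal) of trials; in the pooled sample at about 1.25 d, in about 1–2%. The error figures varied little between the two shapes. The disagreement figures depend on the shape and on the assumed mean of 7 d, and all figures assume complete follow-up. The inflation is moderate and conditional, but the protocol leaves the condition open and the remedy is cheap, so it should be corrected.

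**What to change.** In Section 14.2 name one deciding test per primary outcome before the data analysts are unblinded. One option that fits the planned medians is the Mann–Whitney test stratified by the gestational-age groups used in randomisation (van Elteren), with a matching stratified Hodges–Lehmann estimate and CI. The text should give the cut points of those groups, since Section 5 says only that gestational age is the stratifier. Log-rank as the deciding test would also resolve the point. The essential step is to choose one.

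Label the t-test and whichever of the other two is not chosen as supportive, reported without a claim of significance.

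State how infants without an observed endpoint enter the deciding test. Do not give a blanket worst rank to those who withdraw: Section 15 expects some infants to leave after meconium evacuation and before full feeding, and scoring them as the worst outcome would treat withdrawal as failure.

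Naming the test costs only wording; the stratified version needs a little extra programming. The downside is that the sponsor gives up choosing the test after seeing the data.
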